## Abstract

**Background:**

In general during pregnancy, women are aware of the importance of good diet quality, interested in nutrition, and receptive to changing dietary intake. However, adherence to dietary guidelines is sub-optimal. A pregnant woman’s first information source regarding nutrition information is her midwife. Healthy nutrition promotion by midwives may therefore be very promising, but midwives face multiple barriers in providing nutritional support. Empowering pregnant women to improve their diet quality is expected to improve their health. Therefore an empowerment intervention has been developed to improve diet quality among pregnant women. The objective of this study is to evaluate the effectiveness and feasibility of Power 4 a Healthy Pregnancy (P4HP). P4HP aims to empower pregnant women to have a healthier diet quality.

**Methods/design:**

This study applies a mixed methodology consisting of a non-blinded cluster randomized trial with an intervention (P4HP) group and a control group and a process evaluation. Midwifery practices, the clusters, will be randomly allocated to the intervention arm (*n* = 7) and control arm (*n* = 7). Participating women are placed in intervention or control conditions based on their midwifery practice. Each midwifery practice includes 25 pregnant women, making 350 participants in total. Health related outcomes, diet quality, empowerment, Sense of Coherence, Quality of Life, and Self-Rated Health of participants will be assessed before (T0) and after (T1) the intervention. The process evaluation focuses on multidisciplinary collaboration, facilitators, and barriers, and consists of in-depth interviews with midwives, dieticians and pregnant women.

**Discussion:**

This study is the first to evaluate an empowerment intervention to improve diet quality in this target population. This mixed method evaluation will contribute to knowledge about the effectiveness and feasibility regarding diet quality, empowerment, health-related outcomes, multidisciplinary collaboration, facilitators and barriers of the empowerment intervention P4HP. Results will help inform how to empower pregnant women to achieve improved diet quality by midwives and dieticians. If proven effective, P4HP has the potential to be implemented nationally and scaled up to a long-term trajectory from preconception to the postnatal phase.

**Trial registration:**

The trial is prospectively registered at the Netherlands Trial Register (NL9551). Date registered: 19/05/2021.

**Supplementary Information:**

The online version contains supplementary material available at 10.1186/s12889-022-12543-z.

## Background

A healthy diet is important for everyone, but crucial during pregnancy for the health of both mother and child [1–5]. During pregnancy, women are aware of the importance of a good diet quality and are interested in nutrition [6, 7]. However, adherence to dietary guidelines and recommendations is sub-optimal, especially among pregnant women with lower socioeconomic status (SES) [8–10], and specifically for the intake of fruit, vegetables, grains, folate, and iron [11–15]. Poor diet quality by the mother is associated with adverse health outcomes, including increased risk of pre-eclampsia, gestational diabetes, and excessive gestational weight gain. For the unborn, a poor diet of the mother is related to adverse birth outcomes, including premature birth and low birth weight, as well as disadvantageous health outcomes later in life, such as the increased risk of developing chronic diseases [1–3]. However, due to several challenges, such as nausea, cravings, and ingrained habits, pregnant women experience difficulties with the implementation of dietary changes and sustaining these changes during their pregnancy [8, 16]. On top of that, the diet quality of pregnant women is challenged by aspects such as the costs of living and their physical and social environments.

Pregnancy is often regarded as a critical transition, a teachable moment, in which women are more receptive to changing dietary patterns than in other phases in life [6, 7, 17–19]. Pregnancy might increase awareness regarding diet since women generally feel that one of the few things to positively impact the health of their child is to make dietary improvements [20]. A pregnant woman’s first, most important, and most trusted information source regarding nutrition information is their midwife [6, 7, 21–25]. Also, midwives feel responsible to inform pregnant women about a healthy diet [25]. Compared to other countries, midwives in the Netherlands play a relatively large and central role in maternity care. Healthy nutrition promotion by midwives is therefore promising to make use of this window of opportunity where women are increasingly aware of their behaviours for their health and their child’s health [21, 23, 25, 26]. However, although midwives feel the responsibility to provide nutritional advice, they do not consider themselves nutritional experts and encounter structural barriers in providing nutrition communication [5, 25, 27–29]. Some of the main barriers for midwives are time constraints and unsupportive health systems (e.g. a lack of cooperation with other health professionals) [5, 29–32], as well as limited relevant and reliable resources and training [5, 29, 33–35]. As a result, nutrition communication in antenatal care generally remains suboptimal. Currently, only Dutch women with pregnancy complications, overweight/obesity, or excessive gestational weight gain, or those who asked for it themselves receive comprehensive guidance regarding their nutrition during pregnancy [25, 36, 37].

The modern concept of empowerment is increasingly defined as strengthening the capabilities and the self-reliance of individuals [38]. We use Aubel’s definition, who describes empowerment as ‘the ability of individuals or groups to improve capacities, to critically analyse situations and to take actions to improve those situations’ [39]. This definition applies bottom-up thinking to drive behaviour change [40–42], requiring an environment in which pregnant women can engage in open communication [40]. The process of empowering pregnant women is expected to improve their health, as they are supported to make healthier choices, for example in terms of nutrition [6, 21]. This can therefore result in improved child health and providing children with a healthy and successful start of life [2, 3].

P4HP has been developed in the past years together with stakeholders, aiming to empower pregnant women to have a healthier diet quality [42–45]. This intervention may contribute to enduring new-borns with a healthy, successful start of life [2, 3] and has the potential to improve health across generations. P4HP uses a women-centered empowerment approach, to prioritize the woman’s individual needs, as defined by the woman herself, assigning to the woman’s choice, control, and continuity of care. P4HP allows women to be empowered, gaining control over their lives and learning how to achieve goals that are meaningful to them. Individuals are most likely to change their behaviour to make healthier choices when they are educated and motivated to do so, in addition to environments and policies supporting these decisions [46].

A similar intervention in which empowerment and diet quality among pregnant women is central has not been implemented before to our best knowledge. The research will contribute to theoretical development by providing practice-based evidence [47, 48]. This mixed methods study aims to 1) evaluate the effectiveness of P4HP regarding diet quality, empowerment, Sense of Coherence (SOC), Quality of Life (QoL), and Self-Rated Health (SRH) using a cluster randomized controlled trial (C-RCT), and 2) evaluate P4HP in terms of multidisciplinary collaboration, facilitators and barriers using a process evaluation. This way, as we retrieve both information about what is needed to achieve an effect and about what is needed in the implementation and in the multisectoral collaboration, we gain insight in both the effectiveness as well as the feasibility of P4HP.

Research in the area of empowerment towards dietary intake in pregnancy is sparse [24, 49]. Still, empowerment has been linked to diet quality, although mostly in global south [50–53]. Additional to empowerment and diet quality, health outcomes are included, as empowerment has been previously linked to the concepts QoL [54, 55], SOC [56, 57], and SRH [58, 59]. Also diet quality has been linked to the concepts QoL [60, 61], SOC [62, 63], and SRH [64, 65]. We hypothesize that empowerment, improved diet quality, and the health outcomes QoL, SOC and SRH will have a mutually reinforcing, invigorative effect on each other (Fig. 1).

**Fig. 1 Fig1:**
[figure not shown]
Overview of hypothesis P4HP

## Methods

### Study design

This mixed methods study consists of a non-blinded C-RCT with an intervention (P4HP) group and a control group and a process evaluation. A qualitative process evaluation will take place to evaluate P4HP by midwives and dieticians in terms of multidisciplinary collaboration, facilitators, and barriers.

A pilot study has launched on October 1st, 2021, with the aim to reach a total of 10 participants from two midwifery practices within 2 months. In this pilot study we pre-test the questionnaires, the perceptions of the P4HP intervention, and the practical and technical matters regarding implementation, including the organization of multidisciplinary collaboration. Any suggestions by the midwives, dieticians, and pregnant women will be duly accommodated to improve the feasibility.

### Non-blinded C-RCT

The non-blinded C-RCT will evaluate the effectiveness of P4HP on pregnant women’s empowerment, diet quality, and health outcomes between intervention and control practices. Figure 2 details the flow of participants from recruitment of midwifery practices until the last follow-up contact for intervention and control participants. The clusters are midwifery practices in the Netherlands and the participants are Dutch-speaking pregnant women visiting the practice. Cluster randomization is applied to eliminate the risk of cross-contamination between the two study arms. Thus, whether pregnant women are placed in the intervention or the control group is based on whether receiving care from intervention or control midwifery practices. Due to the nature of the intervention, it is not possible to blind the professionals, participants, or investigators to the study conditions. This protocol has been written according to the recommendations of the Standard Protocol Items Recommendations for Interventional Trials (SPIRIT) 2013 statement [66, 67] (Additional file 1). SPIRIT guides key content to facilitating the drafting of high-quality protocols, including recommendations for intervention trials.

**Fig. 2 Fig2:**
[figure not shown]
Flow diagram of the participants through the trial

### Cluster and participant recruitment

Midwifery practices in the Netherlands will be recruited by using existing connections, snowballing, social media, and presentations of the study at local collaborations of midwifery practices. Midwifery practices are randomized as clusters to either an intervention arm or standard birth care. Clusters will be randomized by a researcher, who is unfamiliar with the midwifery practices, using a randomization scheme in Excel.

Eligible pregnant women will be recruited in randomized midwifery practices (clusters) in the Netherlands using a purposive sampling technique. Midwives will be informed by the research team about the in- and exclusion criteria. Midwives will explore whether or not the pregnant women meet the inclusion criteria and explain to them the purpose of the study. The women will be invited to participate voluntarily. To be eligible to participate in this study, a participant must meet all of the following criteria: being in the first trimester of pregnancy; > 18 years of age; understanding and speaking Dutch; consuming a Dutch diet pattern i.e. a diet with a maximum of one hot meal per day. A potential participant who meets any of the following criteria will be excluded from participation: not willing to provide informed consent; having a severe chronic illness/condition (for example cancer); having conditions that may affect diet quality. The recruitment of participants will begin on 01-01-2022 and will end when all 14 midwifery practices have met their target of 25 women. Alternatively, the recruitment will end on 31-12-2022.

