### Data collection and assessments

At enrolment, participants will give their informed consent through consent forms. Subsequently, participants will be provided with two online quantitative questionnaires to fill out, utilizing baseline data for the study (T0). Upon completion of P4HP, participants are provided the same two online quantitative questionnaires (minus sociodemographic data) to respond to the post-intervention assessment (T1) (Fig. 3). The first questionnaire assesses diet quality [73]. The term diet quality has been used in recent decades to evaluate the dietary habits or patterns of a population and the efficacy of dietary interventions [74–76]. Diet quality is a suitable term to present multiple food components, assessed using an index to evaluate the extent of adherence to dietary guidelines. The second questionnaire includes all other assessments and is distributed using Qualtrics. Access to all data collection tools and databases is strictly limited and regulated through personal user profiles. Both platforms are password-protected and all data will be regularly backed up into a password-protected database.

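### Unblinded midwives recruit women by purposive sampling after their practice is randomised, so randomisation does not guard against selection differences between the women in the two arms

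*Protocol article*

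**What the plan says.** All places are in the protocol article.

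- **Order of events.** Cluster and participant recruitment: "Midwifery practices are randomized as clusters to either an intervention arm or standard birth care". Women are then enrolled inside these practices: "Eligible pregnant women will be recruited in randomized midwifery practices (clusters) in the Netherlands using a purposive sampling technique". The property on which the purposive choice is to be made is not stated.
- **Who recruits.** Same section: "Midwives will explore whether or not the pregnant women meet the inclusion criteria and explain to them the purpose of the study". The research team briefs the midwives on the criteria.
- **Knowledge of arm.** Non-blinded C-RCT: "it is not possible to blind the professionals, participants, or investigators to the study conditions". The abstract (Methods/design) adds: "Participating women are placed in intervention or control conditions based on their midwifery practice". The arm can thus be known before a woman is invited or consents.
- **An open-ended exclusion.** Women are excluded for "having conditions that may affect diet quality". No list of conditions accompanies it.
- **Stopping.** Recruitment "will end when all 14 midwifery practices have met their target of 25 women", or else at the end of 2022.
- **Baseline and adjustment.** Under Data collection and assessments, T0 follows consent. Under Quantitative analyses C-RCT, covariates are identified by testing baseline differences between groups, and the linear mixed model can account for confounders.

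**The concern.** In a cluster trial, randomisation balances the clusters in expectation. It balances the people inside them only if they are identified and enrolled in a way that does not depend on the arm. Here the recruiter knows the arm, and the stated sampling method allows judgement about whom to approach. One eligibility decision also depends on judgement about something close to the outcome.

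What is offered differs by arm. Intervention women are invited to four extra nutrition contacts (Intervention section), control women to usual care (Control section). A midwife might lean towards women who seem motivated, or towards women who seem to need help, and the women's own willingness to join may differ too. The first tendency would probably flatter the intervention and the second could hide a benefit, so the direction cannot be predicted.

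A shift of this kind biases the effect estimate itself, and recruiting more women would not correct it. Once recruitment is complete the selection cannot be undone. Without counts of women eligible and invited it cannot be assessed either.

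**Working it through.** **1. Reproduce the plan's sample size.** Inputs from Sample size estimation: effect 0.4 SD, power 80%, alpha 0.05, ICC 0.02, 7 clusters of 25 per arm. Two-sided testing is stated under Quantitative analyses C-RCT.

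- Design effect = 1 + (25 − 1) × 0.02 = 1.48.
- Effective number per arm = 7 × 25 / 1.48 = 175 / 1.48 = 118.2.
- SE of the arm difference = √(2 / 118.2) = 0.130 SD.
- Degrees of freedom for a cluster-level t-test = 2 × (7 − 1) = 12.
- Non-centrality = 0.4 / 0.130 = 3.08. Power from the non-central t is 80.6%; six clusters per arm would give 72.8%.

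The stated 7 x 25 is reproduced, so the same SE and degrees of freedom can be used below.

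**2. Effect of a selection shift.** Let b be the part of the arm difference, in SD units, that comes from selection and remains after any adjustment for T0 and covariates. The documents give no value for b, so every value here is an assumption. With no true effect, the chance of p < 0.05 is the two-sided non-central t probability with 12 df and non-centrality b / 0.130. When the shift works against a true effect of 0.4, the difference available to detect is 0.4 − b.

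| Assumed b (SD) | Share of 0.4 target | False-positive rate | Power if the shift opposes a true 0.4 |
|---|---|---|---|
| 0 | 0% | 5.0% | 80.6% |
| 0.05 | 12.5% | about 6% | 69.6% |
| 0.10 | 25% | 10.9% | 56.4% |
| 0.15 | 37.5% | 18.6% | 42.4% |
| 0.20 | 50% | 29.4% | 29.4% |

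**3. What the existing safeguards cover.**

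- A researcher unfamiliar with the practices does the randomising. This protects the allocation of practices, not the later choice of women.
- T0 is taken after consent, so it describes women who have already been selected. It helps with differences in baseline level, but not with differences in readiness to change beyond what T0 captures.
- The assessments listed contain no measure of motivation to change diet. The empowerment scale and the T0 diet score may be partial proxies.
- Choosing covariates by baseline significance tests is a weak filter: an imbalance that matters can fail to reach significance.

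**The case against.** **Purposive may be loose wording.** It may mean no more than recruiting women who meet the criteria. The same criteria apply in both arms, and the midwife's stated task is to check them and explain the study. The Discussion also says that all SES groups visiting participating practices will be included. This has force: a reader might infer that midwives choose freely among eligible women, and the text does not say so outright. But the Process evaluation section plans a purposeful sample for the interviews, where that suits the aim, and the recruitment section applies the same idea to the trial. If it is meant, it permits arm-dependent selection. If it is not, the sentence misstates the method. Either way it should change.

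**Room and incentive to select.** A reader might infer that 25 women per practice in up to a year leaves ample room to choose, or that control midwives have no reason to select. The documents give no caseload, uptake or eligible fraction, and say nothing about incentives. The fallback closing date shows that the sponsor allows for practices missing their target. Neither inference is relied on here.

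**Adjustment.** T0 is measured for the outcomes and the model can take in covariates, so much of a shift in baseline level may be absorbed. That stands, and it is why b is defined as what remains after adjustment.

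**A condensed article.** Screening logs and detailed exclusion lists may be in the full protocol, and the flow diagram and SPIRIT file are not shown. Their absence is not the point. The point is the sampling rule that the article states.

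**Recruitment after allocation is partly unavoidable.** Women enter in the first trimester over as long as a year. That is a reason to make the invitation rule mechanical.

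**Conclusion.** The point holds in this form: a stated rule lets unblinded recruiters select women after allocation, so randomising practices does not protect against differences between the women in the two arms. A reader might go further and infer that randomisation no longer protects the comparison at all. The documents do not support that, because the practices remain randomised and bias among the women is possible rather than shown.

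The table of error rates is an illustration, not a forecast. It rests on an assumed residual shift, the stated ICC of 0.02, equal clusters of 25 and a 12-df test. Under those assumptions a residual shift of a quarter of the target effect roughly doubles the false-positive rate, to about 11%. The same shift in the other direction lowers power from about 81% to 56%.

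**What to change.** In Cluster and participant recruitment, drop purposive sampling for the trial and keep it for the interviews. State instead that each practice, in both arms, invites every consecutive woman who meets the criteria, from a set start date until 25 have consented or recruitment closes.

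Two supporting steps:

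- Use equivalent, neutrally worded study information in both arms, consistent with the consent requirements. Having women complete T0 before the programme is described is not advised. Ethical consideration requires consent after the study's purpose and possible consequences have been explained, and T0 comes after consent.
- Keep a tally per practice of women eligible, invited and consented, and report it by arm.

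The cost is a rewritten recruitment sentence, a check of the study information and a short tally sheet per practice. Midwives lose the choice of whom to invite. Women still know their arm when they decide, so differential consent is reduced, not removed; the tally would at least show how far uptake differs between arms.

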### Sample size estimation

The sample size estimation is based on the design of a C-RCT [68] using the Group-or Cluster-Randomized Trials sample size calculator from the National Institutes of Health [69], where each cluster represents a midwifery practice. The results indicate that to detect an effect size of 0.4 (small to medium) [70] with a power of 80%, an alpha of 0.05, and an intra-cluster correlation coefficient of 0.02, each arm should include 7 clusters of 25 participants each. The assumption of an intra-cluster correlation coefficient of 0.02 is based on our experience with the SLIMMER project, a cluster randomized trial of a combined lifestyle intervention including behaviour change in diet and physical activity on overweight and risk of diabetes [71]. We strive to keep the number of participating pregnant women per cluster as similar as possible. Based on the sensitivity analysis for this sample size estimation [69], we estimate that 25 participants from 7 intervention and 7 control clusters – leading to 350 participants in total – will be sufficient to detect the relevant difference between groups. The Netherlands had 168.066 births in the year 2020 [72]. Three hundred fifty participants represent < 0.25% of pregnancies in the Netherlands, and therefore expected to be achievable.

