### Ethical consideration

Ethics approval was given by Medical Research Ethics Committee Utrecht, the Netherlands on September 21st 2021. The committee thereby declares that the proposal satisfactorily deals with ethical issues and that it complies with the Netherlands Code of Conduct for Scientific Practice. Because of negligible risk for participants, the MREC Utrecht has granted this study exemption from the obligation to the insurance that covers damage caused by the research through injury of the participant. Therefore, adverse events are currently not foreseen, due to the nature of the study and intervention. Informed consent will be obtained from each participant, after the purpose and possible consequences of the study have been explained. This study will be conducted according to the principles of the Declaration of Helsinki (October 2013) and according to the Medical Research Involving Human Subjects Act (WMO).

Participation in the study is voluntary and participants can leave the study at any time for any reason if they wish to do so without any consequences. They are asked to inform either the principal investigator or intervention deliverer (midwife or dietician) about their decision. Participants are not obliged to inform the researchers about their reason to withdraw. The investigator can decide to withdraw a participant from the study for urgent medical reasons, such as having a miscarriage or a pregnancy with extreme complications. The reason for withdrawal reason will be kept for the record for further study. Since P4HP is possibly delivered in a group format, there will be no replacement of individual participants after withdrawal.

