Self-Rated Health *(GSRH)* Intervention (n=) Control (n=) Effect size					

Linear mixed models will be used to analyse the data. Using linear mixed models allows for the analysis of different sources of variation in data and for unequal variances and correlations. This flexible method is suitable for analysis of the clustered data as it allows to calculate the treatment effect. When there are multiple levels, such as pregnant women seen by the same midwifery practice, the variability in the outcome can be thought of as either within-group or between-group. Pregnant women-level observations are not independent, as within a midwifery practice pregnant women and their guidance are more similar. Units samples at the highest level (in our research, midwifery practices) are regarded as independent. With this method also confounders can be taken into account [102]. After performing the linear mixed models analysis, the final results will be presented in Table 3. This table will display means and standard errors, the between-group differences, and the *p*-values for the treatment effect for all primary and secondary outcomes.

All primary and secondary outcomes will be tested via linear mixed models. Other subgroup analyses include age, ethnicity, individual or group (CenteringPregnancy) consultation, educational level, living situation, working situation, and income level. These variables will be checked if they differ across the groups using an independent Student’s t-test when continuous and normally distributed. If skewed, a Wilcoxon signed-rank test will be done. Variables that are not continuous, will be checked for differences between groups using a chi-square test. Two-sided *p* values < 0.05 will be regarded as statistically significant.

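### The 25 women per practice that the power calculation needs at analysis is also the enrolment target, so 80% power has room for only about 2% loss before T1

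*Protocol article*

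**What the plan says.** Under Sample size estimation, the article plans for a standardised effect of 0.4 "with a power of 80%, an alpha of 0.05" and an intra-cluster correlation of 0.02, and reports the calculator's result: "each arm should include 7 clusters of 25 participants each". It concludes that the resulting total of 350 is sufficient. No allowance for loss is mentioned.

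Under Cluster and participant recruitment, women enter in the first trimester, and recruitment "will end when all 14 midwifery practices have met their target of 25 women", or at the end of 2022 as an alternative.

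Under Ethical consideration, women may leave at any time, the investigator may withdraw a woman "for urgent medical reasons, such as having a miscarriage or a pregnancy with extreme complications", and "there will be no replacement of individual participants after withdrawal". The reason given for the last rule is the possible group format.

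Under Data collection and assessments, T1 follows completion of P4HP, and Table 1 places the last session at about 32 weeks. Quantitative analyses C-RCT expects some missing data, plans linear mixed models on all available T0 and T1 data, and sets the test level: "Two-sided *p* values < 0.05 will be regarded as statistically significant".

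**The concern.** The same number does two jobs. In the calculation, 25 is the number of women per practice who contribute to the between-arm comparison. In the recruitment rule, 25 is the number enrolled. The two agree only if nearly everyone enrolled in the first trimester reaches T1 in late pregnancy, and the article itself expects that some will not.

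If the 25 contained a margin for loss, this would not matter. If it contains none, the stated power describes a larger analysed sample than the enrolment and withdrawal rules are likely to produce. A null result would then be read against a somewhat overstated figure for the trial's ability to detect 0.4 SD.

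**Working it through.** **Inputs from the article.** Effect d = 0.4; power 80%; alpha 0.05; ICC = 0.02; k = 7 practices per arm; m = 25 women per practice. The sample size section does not state sidedness; two-sided is taken from the analysis section.

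**Assumed.** Loss of 10%, 20% or 30% before T1, spread evenly over practices. The article gives no rate.

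**Formulae.**
- Design effect: DE = 1 + (m − 1) × ICC
- Standard error in SD units: SE = √(2 × DE / (k × m))
- Non-centrality: ncp = d / SE
- Power: two-sided non-central t on 2 × (k − 1) = 12 df
- Detectable effect at 80% power: (2.179 + 0.873) × SE, from the 97.5% and 80% points of t on 12 df

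**Reproducing the stated figure.** With m = 25, DE = 1 + 24 × 0.02 = 1.48; SE = √(2 × 1.48 / 175) = 0.130; ncp = 0.4 / 0.130 = 3.076 (unrounded SE); power = 80.6%. This matches the stated 80%. Two variants do not: the normal approximation gives 86.8%, and a one-sided t test gives 89.4%. With 6 practices of 25 per arm, power is 72.8%, so 7 is the smallest number of practices that works.

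**Letting the analysed number fall.**

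| Analysed per practice | Loss | DE | ncp | Power | Detectable effect (SD) |
|---|---|---|---|---|---|
| 25 | 0% | 1.48 | 3.076 | 80.6% | 0.40 |
| 24 | 4% | 1.46 | 3.034 | 79.5% | 0.40 |
| 22.5 | 10% | 1.43 | 2.968 | 77.8% | 0.41 |
| 20 | 20% | 1.38 | 2.849 | 74.4% | 0.43 |
| 17.5 | 30% | 1.33 | 2.714 | 70.3% | 0.45 |

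Among whole numbers, 25 is the smallest cluster size that reaches 80%.

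**Margin.** Power equals exactly 80% at m = 24.44, a loss of 0.56 × 14 = 7.8 women, or 2.2% of 350. Losing 7 women leaves 343 (24.5 per practice) and about 80.1% power.

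**What T0 adjustment could recover.** If adjusting for the T0 value multiplies the variance by 1 − r², with r the T0–T1 correlation and the same reduction between and within practices, then at m = 20 power is 78.3%, 81.4% and 85.5% for r = 0.3, 0.4 and 0.5. The correlation needed to return to 80% is about 0.23 at 10% loss, 0.36 at 20% and 0.46 at 30%. The article gives no correlation, so these values are assumptions.

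**Unequal practices.** With an assumed coefficient of variation of 0.3 in cluster size and no loss, DE = 1 + (1.09 × 25 − 1) × 0.02 = 1.525 and power is 79.4%. Uneven recruitment or loss would therefore use up the margin by itself.

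**The case against.** The strongest reply is that nothing has been miscalculated: the stated inputs give the stated power. That is right. The fault lies in how the sample size, recruitment and withdrawal rules fit together.

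A second reply is that the planned analysis is stronger than the unadjusted comparison used above. The same instruments are given at T0 and T1, mixed models are planned, and confounders can be included. A modest T0–T1 correlation would make up a 20% loss. This stands as a possibility. But the sample size section claims no such gain, and the analysis section does not say that T0 enters as a covariate, so neither the recovery nor the shortfall is certain.

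A third is that a normal approximation gives 86.8% and would tolerate about 24% loss. The calculator's settings are not reported, but that method does not reproduce the stated 80%, and it ignores that there are only 14 practices.

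A fourth is that the recruitment sentence sets a target for ending recruitment across the trial rather than a ceiling within each practice. Read literally, it does. However, the abstract and the sample size section both put the total at 350, so no overshoot is planned. The alternative end date can only lower the number.

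Lastly, a condensed article may leave an attrition allowance to the full protocol. Loss may indeed have been considered there. It remains that the article gives 25 both as the number required and as the number enrolled.

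**Conclusion.** The point holds with moderate size. The stated 80% rests on about 25 analysed women per practice, and the recruitment and withdrawal rules are unlikely to deliver that number. The tolerance is about 2%. Beyond it, the unadjusted shortfall from 80% is about 2 points at 10% loss, 6 at 20% and 10 at 30%. These figures depend on an assumed loss rate, even loss across practices, an ICC of 0.02 and no use of T0.

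A reader might infer more: that 80% power requires T1 data from all 350 women, that any loss at all breaks it, or that the trial never had the stated power. The documents support none of these. Seven women can be lost, full follow-up gives 80.6%, and a T0-adjusted analysis might restore the figure. It should be fixed, but it does not undermine the design.

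**What to change.** In Sample size estimation, describe 25 as the number enrolled per practice, state an expected loss before T1 with its basis, and give the power or detectable effect for the number expected to be analysed. For example, with an assumed 20% loss, 20 women per practice are analysed, unadjusted power for 0.4 SD is 74%, and the effect detectable at 80% power is 0.43 SD.

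In the same place and in Quantitative analyses C-RCT, name the linear mixed model adjusted for the T0 value of the outcome as the analysis. Add that, at 20% loss, it would bring power back to about 80% if the T0–T1 correlation is about 0.36 or higher, and label that correlation as an assumption.

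The cost is a few sentences and a slightly less favourable stated figure. No extra women are needed. Keeping 25 analysed by enrolling more would cost much more: at 20% loss, 25 / 0.8 = 31.25, so 32 per practice and 14 × 32 = 448 in total.
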